	**End of rehabilitation and start intervention**
T1	After patients have completed rehabilitation the intervention starts
T2	After 8 weeks the intervention is completed
	**End of the intervention period**
	**Waiting list control group starts intervention**
T3	4 week follow-up measurement
T4	6 month follow-up measurement
T5	12 month follow-up measurements

### Participants and recruitment

Participants will be recruited in cardiac rehabilitation facilities in Germany and the Netherlands*.* The study population will consist of people aged up to 85 years who successfully completed cardiac rehabilitation. In order to be eligible to participate in this study participants need to be able to use a computer, familiar with the use of the Internet, and need sufficient reading and writing language skills in the relevant language (German or Dutch). Patients with contraindications for physical activity and fruit and vegetable consumption will be excluded (e.g., heart failure patients which are not allowed to eat 2 pieces of fruit per day [5]).

### Power analysis

The power analysis was based on the assumption that the intervention will result in a small improvement of effect to improve fruit and vegetable consumption and in a small to medium effect to improve physical activity for the study conditions [38]. The calculation was based on an effect size of 0.3, with a power (1-β) of 0.8 and alpha of 0.05.

No cluster effect is expected due to the fact that the randomization of the participants is independent of the place of recruitment. Further, it is necessary to take interaction effects into account between the intervention and the control group, and between Germany and the Netherlands.

Therefore, to be able to detect a small to medium effect, 263 people have to participate in every group in each country. This means that the required total sample size will need to consist of 1052 participants, not adjusted for potential drop out during the intervention.

### Randomization

During the rehabilitation period, patients will be recruited within the rehabilitation center by their therapists. These therapists will first inform the person undergoing rehabilitation about the study and hand out study information. Participants will log in on the project website and have to give online informed consent. Randomization will be done by the computer software *TailorBuilder*, which is developed for internet based tailored interventions. Participants will be randomly allocated to the study group or to the waiting list control group. The waiting list control group will get access to the intervention after eight weeks (see Table 1).

### Intervention

The Health-Action Process Approach (HAPA) will be used as a theoretical framework to develop the intervention [52,53]. The HAPA Model distinguishes two phases during the process of behavior change: a motivational phase in which the intention to perform a specific behavior is formed and a volitional phase in which the intention is translated into the actual performance of the behavior. Depending on the stage, people have different needs. Within the motivational phase positive outcome expectancies, a high risk perception and a high self-efficacy to perform the specific behavior are necessary to develop an intention. Once people have formed the intention to perform a certain behavior, skills such as action and coping planning, self-efficacy, and social support are necessary. The HAPA Model further distinguishes between stages of intention. Non-intenders are in the motivational phase and have no intention to change their behavior. Intenders are in the volitional phase but do not perform the behavior in contrast to actors, who carry out the behavior [52]. The intervention will target the concepts of the different stages via the use of behavior change techniques. In line with Abraham and Michie [54], we use several behavior change techniques like providing information about behavioral risk and benefit of behavior change, prompting intention formation, prompting barrier identification, providing instructions how to perform a behavior, prompting specific goal setting and review of behavioral goals, providing feedback on performance, prompting practice and providing follow-up prompts, prompting to plan social support and finally prompting relapse prevention, also based on strategies used by other effective computer tailoring programs [55,56].

During the eight-week intervention period, participants will be invited to access the online program once per week and take part in one of the intervention modules. These eight modules aim to increase participants´ risk perception of CVD, support positive outcome expectancies towards physical activity and fruit and vegetable consumption, and guide participants in defining and reflecting on their own goals, action plans and coping plans. Further, self-efficacy regarding the participant’s ability to perform and maintain the two targeted behaviors will be addressed.

Table 2 presents a short overview about the weekly intervention content. During the first session, participants will receive feedback and information about their risk perception, outcome expectancies and their behavior with regard to physical activity and fruit and vegetable consumption which is based on the previous assessment. During the following session, participants formulate their own individual goals and specific plans with regard to physical activity and fruit and vegetable intake. Participants will receive information about how to structure a plan as good as possible. For example *“I would like to go for a walk in the park for 30 minutes each Tuesday.”* All plans have to be evaluated with regard to their feasibility through self-reflection. This will be achieved by asking the participants questions like: *“Is your plan ‘to go for a walk in the park’ easy to implement into your daily routine?*”

**Table 2 T2:** Intervention content

**Weekly sessions**	**Weekly content**
Session 1 PA and Session 5 F&V	Questionnaire and personalized feedback, increase risk perception and outcome expectations, defining own health outcomes; (Session 5: Assessment of social cognitive factors)
Session 2 PA and Session 6 F&V	Personalized feedback, defining action plans
Session 3 PA and Session 7 F&V	Personalized feedback
	Evaluation and self-reflection about action plans
	Adjusting action plans
	Defining personal barriers
	Develop personal coping plans
	Evaluation and refection about coping plans
Session 4 PA and Session 8 F&V	Personalized feedback, adjusting coping plans, thinking about social support and development of a list of potential supporters from the social environment; (Session 8: T2 questionnaire)

**(PA)** physical activity; **(F&V)** fruit and vegetable consumption.

After reviewing the plans, participants get the opportunity to adjust them. After each session, participants will be motivated to practice their plans. During the next session, participants are asked to evaluate their action plans and if necessary adjust them. People who indicate to have problems formulating plans will receive role model examples. Furthermore, they are asked to identify their personal barriers and obstacles that prevent them from putting plans into practice. Barriers need to be defined and participants are again asked to define plans on how to deal with those plans. For example, if someone chooses “*It is difficult for me to eat fruit and vegetables when I am not at home*”, the person will be asked to think about a strategy to be able to eat fruit and vegetable like *“when I leave the house for some hours I will take an apple with me”*. Defining action and coping plans has been proven to be an effective tool to increase physical activity among cardiac rehabilitation patients [57]. Again, these coping plans have to be evaluated during the next session and can be adjusted if necessary. During the last session of each behavior, participants will be asked to think about persons in their social environment who could be able to support their change and can be useful to help them.

The intervention will be enriched by different kinds of feedback: ipsative feedback will be used to provide participants with an overview of their development with regard to physical activity and fruit and vegetable consumption [41,58,59]. At the beginning of each session participants will be asked about the physical activity or fruit and vegetable consumption during the preceding seven days. After that, they will receive tailored feedback about their behavior.

Normative feedback will be provided to give information about whether the behavior meets the recommendations for both target behaviors [42,56]. Feedback will not only be based on the assessment at the beginning of the intervention T1 but also given dynamically with the use of information that will be assessed during the intervention. In this way the feedback is based on the newest information and contains more relevant information. *“Ben, you ate 3 portions of fruit and vegetable per day. This is a bit more than the last time. Great! But remember, it would be good for you to eat at least 5 portions fruit and vegetable a day. RENATA can support you to achieve this goal.”* In addition, a figure (see Figure 1) will present the prior behavior, the behavior of the past weeks, and whether participants fulfill the recommended amount of physical activity or fruit and vegetable consumption.

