### Study design

This multinational and multicenter longitudinal study has a quasi-experimental randomized controlled trial design. The study consists of one intervention group (IG) and one waiting list control group. The intervention group will first address physical activity then fruit and vegetable consumption. The waiting list control group will get access to the intervention after the study condition has finished the intervention (T3). The waiting list control group has to complete the baseline questionnaire (T1) at the same time as the intervention group and will have access to the intervention only after their second measurement. In total, six data collection time points are planned where T0 is intended for the collection of contact information only. Baseline measurement will take place at T1 before the intervention starts, followed by a measurement (T2) after completion of the intervention. Further follow-up measurements are planned to take place after four weeks (T3), after six months (T4) and after 12 months (T5) (see Table 1).

**Table 1 T1:** Design of measurement points

**Time point**	**Measurement**
T0	Patients within cardiac rehabilitation will be asked if they are interested in participation of an aftercare program. Contact data will be collected

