### Statistical analysis

Descriptive statistics will be used to describe baseline characteristics of the study. We will assess whether there are significant differences between the intervention group in comparison with the control group according to physical activity and nutrition by means of linear regression analysis in PASW (SPSS). The pre-test and post-test measurements of the control group will be compared with the measurements of the intervention and controle group with regard to the target behaviours.

To be able to assess the impact of the intervention on the performance of physical activity and fruit and vegetable consumption, we intend to perform several analyses of covariance (ANCOVA) after four weeks (T3) and six months (T4), controlling for the baseline performance. Multivariate regression analysis will be used to determine possible confounding or modification effects. Regression analysis will allow us to identify the percentage of variability of the dependent variable that is explained by the determinants used. In order to detect differences between the study condition and the control group, effect sizes will be calculated for each study group separately [78].

Subgroup analyses will be performed to determine if the benefit of the intervention depends between groups like nationality or socioeconomic status [79]. Further, dose–response-analyses will be conducted with logistic regression to see if the intervention effect depended on the time spent on the webpage.

Baseline characteristics of participants who dropped out will be compared with participants who finished the intervention to examine whether drop out is at random or determined by specific characteristics.

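### The intervention arm's T2 questionnaire sits inside Session 8, so T2 response may depend on adherence in that arm only and may bias the immediate post-intervention comparison

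*Protocol article*

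**What the plan says.** T2 is anchored in two ways. Study design ties it to finishing the programme: "followed by a measurement (T2) after completion of the intervention". Table 1 ties it to the calendar: "After 8 weeks the intervention is completed". The two coincide only for someone who keeps to schedule. Table 2 then lists the questionnaire as part of the final fruit-and-vegetable module: "Session 8: T2 questionnaire".

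Sessions are offered weekly: "participants will be invited to access the online program once per week and take part in one of the intervention modules". The article does not say that a later session stays closed until earlier ones are done. It also does not describe a T2 request that reaches people who have stopped.

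Controls have no sessions before T2. On when they get the programme, the article is not consistent:

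- Study design, first statement, labelled T3: "will get access to the intervention after the study condition has finished the intervention (T3".
- Study design, second statement: "will have access to the intervention only after their second measurement".
- Table 1, between T2 and T3: "Waiting list control group starts intervention".
- Randomization: after eight weeks, with a reference to Table 1.

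Statistical analysis names ANCOVAs at T3 and T4, adjusted for baseline. T2 is covered at most by a general sentence on pre-test and post-test measurements that names no time point. On attrition it says: "Baseline characteristics of participants who dropped out will be compared with participants who finished the intervention to examine whether drop out is at random".

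**The concern.** If T2 is delivered only through Session 8, an intervention participant must persist to the eighth module to supply the outcome, while a control need only answer a questionnaire. The comparison then sets programme completers against nearly all controls. Completers are plausibly more motivated, which would favour the programme. Adjusting for baseline behaviour removes only the part of motivation that baseline behaviour captures.

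T2 matters because, on Table 1, Randomization and the second-measurement sentence of Study design, controls receive the programme right after it. On that reading T2 is the only comparison with untreated controls, and later time points compare immediate with delayed access.

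The drop-out comparison would not reveal the problem. Finishing the intervention is not defined for controls before T2, and stopping the modules is merged with missing an outcome. Similar baseline characteristics cannot show that drop-out is at random, since missingness may depend on outcomes that were never observed.

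**Working it through.** **What the document supplies.** It gives no completion or response rate, so there is no figure of the plan to reproduce on this point. Power analysis gives an effect size of 0.3 and 263 participants per group per country, not adjusted for drop-out. Pooled over countries this is 2 × 263 = 526 per arm.

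**Assumptions (none is in the document).** No true effect; outcome SD 1; correlation of outcome with baseline r = 0.5; baseline-adjusted comparison at T2; share c of the intervention arm reaching Session 8; correlation ρ between the propensity to complete and the baseline-adjusted outcome.

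**Formula.** A person responds when a normal propensity exceeds a threshold z passed with probability c. The mean excess among responders is

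bias = ρ × φ(z)/c × √(1 − r²), with √(1 − 0.25) = 0.866.

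**Full control response.** φ(z)/c is 0.350, 0.644, 0.798 and 0.966 for c = 80, 60, 50 and 40%.

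| Reach Session 8 | ρ = 0.1 | ρ = 0.2 | ρ = 0.3 |
|---|---|---|---|
| 80% | 0.030 | 0.061 | 0.091 |
| 60% | 0.056 | 0.112 | 0.167 |
| 50% | 0.069 | 0.138 | 0.207 |
| 40% | 0.084 | 0.167 | 0.251 |

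The central case is 0.644 × 0.2 × 0.866 = 0.11 SD, a little over a third of 0.3 (0.112/0.3 = 37%). The grid runs from 0.03 to 0.25 SD. At ρ = 0 every entry is zero and only precision is lost.

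**Controls also drop out, with the same selection.** The bias is then the difference between the arms. At ρ = 0.2 and 60% intervention response:

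- 80% of controls respond: 0.112 − 0.350 × 0.2 × 0.866 = 0.112 − 0.061 = about 0.05 SD.
- 90% of controls respond (φ(z)/c = 0.195): 0.112 − 0.034 = about 0.08 SD.

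**Effect on a two-sided 5% test, 526 randomised per arm, ρ = 0.2, 60% intervention response.** The factor 0.866 cancels between bias and standard error.

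- Full control response: 0.129/√(1/526 + 1/315.6) = 0.129/0.0712 = 1.81, so about 44% of null trials reject.
- 80% control response: (0.129 − 0.070)/√(1/420.8 + 1/315.6) = 0.059/0.0745 = 0.79, so about 12% reject.

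**The case against.** The strongest reply is that Table 2 is an overview of weekly content. It may show only that T2 falls in the week-8 contact, not who is allowed to answer. Table 1 dates T2 by calendar, nothing locks Session 8, and how non-completers are followed up is detail that an article may leave to the full protocol. This stands against a stronger reading that a reader might infer, namely that early stoppers have no T2 outcome. The article does not say so. It does state an arm-specific route to T2, which is more than silence.

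A reader might also infer that the planned ANCOVAs are biased. They are named at T3 and T4, and nothing ties those measurements to a session, so that inference is not supported. The bias worked out above applies to a T2 comparison that the article mentions only in general terms.

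A third tempting reading is that T2 is certainly the only comparison free of contamination. The sentence labelled T3 in Study design conflicts with this: taken literally, T3 could also be untreated for controls. The statements on control access must be reconciled.

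Finally, full control response is the choice most favourable to the concern, and relaxing it can halve the figure. Missing-data methods may also sit in an analysis plan that is not shown, so their absence here is no fault. The objection to the drop-out sentence remains, because its stated purpose cannot be met by a baseline comparison.

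**Conclusion.** The point holds in a limited form. As written, the intervention arm's T2 collection is tied to the last module and the controls' is not, so response may depend on adherence in one arm only. This may bias the immediate post-intervention comparison, provided that stopping is related to outcome. Completion rates, the correlation and its sign, the baseline correlation and control response are all assumptions, so the sizes above illustrate what is possible and do not estimate what will happen. The upper part of the range would be material against an effect of 0.3, and the lower part would not. Because neither missing T2 data for early stoppers nor a T2 ANCOVA is stated, this ranks as a change that should be made, below must-fix.

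**What to change.** - In Study design and Table 2, separate T2 from Session 8. State that every randomised participant receives the same T2 questionnaire, with the same invitation and reminders, at week 8 from T1 whatever modules were done.
- In Statistical analysis, state that the T2 comparison analyses participants as randomised.
- Replace the comparison of drop-outs with programme finishers by a comparison, within each arm, of participants with and without the outcome. Remove the inference that drop-out is at random.
- Reconcile the statements on when controls get access, so that it is clear which time points compare with untreated controls.

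The cost is a scheduling change in the existing software and a few sentences. The downside is that some T2 answers will come from people who have not finished the modules, which is what an analysis as randomised requires. The change should be in place before enrolment, since T2 answers not collected at week 8 cannot be recovered later.

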### Past health behavior

The level of physical activity will be assessed with the use of the short version of the International Physical Activity Questionnaire (IPAQ) [62]. Participants will be asked to estimate how many days during the past seven day they were vigorous and moderate physically active. Further, the amount of days and spend time for walking during the past seven days will be asked. The IPAQ is a valid measurement instrument which allows an international comparison of participant’s physical activity level.

To assess the fruit and vegetable consumption during the past seven days, four items will be used. Participants will be asked to count the number of consumed portions or glasses fruit and vegetable a day. It will be distinguished between fruit, fruit juice/vegetable juice, cooked or steamed vegetable, and salad and raw vegetable [63].

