### Main study outcomes

The primary study parameter of this study is to analyze the effectiveness of a rehabilitation aftercare program with regard to the level of physical activity and fruit and vegetable intake. The effect of the program will be compared between the intervention group and the control group as well as between the different countries. Secondary study parameters that will be investigated are self-efficacy, outcome expectations, habit, compensatory cognitions, social support, action and coping planning, intention to change, duration absence from work, quality of life and wellbeing. The other study parameters which will be considered are demographic variables, socioeconomic status, stage, age, gender, depression, and health status.

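### As written, the intervention arm can answer the T2 fruit-and-vegetable items just after feedback on the same week's intake; controls get no such feedback, so the items should come first in Session 8

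*Protocol article*

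**What the plan says.** Main study outcomes sets the primary aim: to "analyze the effectiveness of a rehabilitation aftercare program with regard to the level of physical activity and fruit and vegetable intake". Past health behavior shows that both are self-reports over the past seven days. For physical activity, with the short IPAQ: "Participants will be asked to estimate how many days during the past seven day they were vigorous and moderate physically active". For diet, with four items: "Participants will be asked to count the number of consumed portions or glasses fruit and vegetable a day". The article lists no objective measure of either.

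The Intervention section describes how each weekly session opens: "At the beginning of each session participants will be asked about the physical activity or fruit and vegetable consumption during the preceding seven days". It continues: "After that, they will receive tailored feedback about their behavior". The example message praises a higher value than last time and recalls the five-portion target. A figure then shows earlier values and "whether participants fulfill the recommended amount of physical activity or fruit and vegetable consumption".

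Table 2 assigns Sessions 1 to 4 to physical activity and Sessions 5 to 8 to fruit and vegetables. The Session 8 row lists personalised feedback and planning content and ends with "Session 8: T2 questionnaire". Study design places T2 after the intervention has been completed.

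Controls complete T1 at the same time as the intervention group and "will have access to the intervention only after their second measurement". Table 1 puts their start at T2.

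**The concern.** The outcome question and the programme's own feedback question cover the same behaviour over the same seven days. If the feedback comes between them, an intervention participant reports the week's fruit and vegetable intake, is shown how that report compares with past values and the recommendation, and then reports the same week again as trial data. A control answers the trial items with no personal feedback beforehand.

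Any pull of the second answer towards the target, or towards consistency with the graph, then exists in one arm only. In the data it looks the same as a change in behaviour. Randomisation does not protect against it, because it arises after allocation. Adjustment for T1 does not remove it, because T1 precedes the feedback in both arms.

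Under Table 1, T2 is the only post-baseline measurement before controls start the programme, so it is the cleanest comparison of programme with no programme.

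**Working it through.** **1. Where T2 falls in Session 8.** Three statements bear on this.
- Intervention section: the seven-day recall comes at the start of every session, and feedback follows.
- Table 2: the T2 questionnaire is the last entry in the Session 8 row.
- Study design: T2 follows completion of the intervention.

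Together they most naturally give recall, feedback, session content, then T2. No sentence states the screen order outright.

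**2. Which outcome is exposed.** Session 8 is the fourth fruit-and-vegetable session, so same-session feedback concerns that outcome. Physical-activity sessions end with Session 4, which at one session per week is 8 − 4 = 4 weeks before Session 8.

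**3. Which analyses are exposed.** Statistical analysis names ANCOVAs at T3 and T4, and also an undated pre-test/post-test comparison of the target behaviours that appears to use T2. On Table 1 timing and the same weekly order, controls at T3 are about four sessions in. They have reached the physical-activity sessions but not Sessions 5 to 8. Repeated fruit-and-vegetable feedback therefore still differs by arm at T3, though in the intervention arm it is no longer from the same session. By T4, controls who took up the programme have had the same kind of feedback.

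**4. What is lost by asking first.** Nothing shown in Session 8 can alter intake in the seven days before it. Moving the T2 items ahead of the feedback therefore removes no real effect from the measurement.

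**5. Illustration of size.** The plan gives no figure for reporting bias, so there is none to reproduce. Inputs from Power analysis: effect size 0.3 (taken here as a standardised mean difference), alpha 0.05 (taken as two-sided), 263 per group per country, hence 2 × 263 = 526 per arm with both countries pooled. How 263 was derived is a separate matter; it is used here only as the planned size.

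Let b be an assumed arm-specific reporting shift in SD units, with no true effect, complete data and an unadjusted comparison. Then

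P(p < 0.05) = 1 − Φ(1.96 − b/√(2/n)) + Φ(−1.96 − b/√(2/n)).

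For n = 526, √(2/526) = 0.0617. With b = 0.10: 0.10/0.0617 = 1.62, and 1 − Φ(0.34) = 0.37. With b = 0.20: 0.20/0.0617 = 3.24, and 1 − Φ(−1.28) = 0.90. The lower tail is negligible in both.

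| Assumed shift b (SD) | b / 0.3 | 526 per arm (pooled) | 263 per arm (one country) |
|---|---|---|---|
| 0 | 0% | 5% | 5% |
| 0.05 | 17% | 13% | 9% |
| 0.10 | 33% | 37% | 21% |
| 0.15 | 50% | 68% | 41% |
| 0.20 | 67% | 90% | 63% |

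The last two columns give the chance of a significant result with no change in behaviour. They show what a shift of a given size would do, not that one occurs. They refer to the whole reporting shift at T2; the share due to same-session feedback is unknown.

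**The case against.** The strongest reply is that the article never states the screen order. The T2 items could themselves be Session 8's opening recall, much as Session 1 combines questionnaire and feedback, and a journal article may leave such detail to the full protocol. That is fair as to certainty. But the article does place T2 in a feedback session, lists it last, and defines it as after completion. The point concerns what that text implies.

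A second reply is that feedback is the active ingredient, so its influence cannot be separated from the treatment. This holds for Sessions 1 to 7, whose feedback precedes T2 whatever the order. It does not hold for Session 8, which cannot change the week already past.

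A reader might infer more than the documents support:
- *That controls have met no norm before T2.* Questionnaire items on intention, stage, self-efficacy, outcome expectancies and habit name the five-portion or five-days-of-30-minutes targets. What controls lack is praise, comparison with their own reports, and the graph.
- *That controls understate their behaviour because T2 opens the programme.* The article gives only the timing of access. Nothing makes access depend on the answers or suggests that controls think so.
- *That both primary outcomes are equally affected.* The session order does not support this.
- *That the T3 and T4 ANCOVAs carry the full bias.* Under Table 1 they do so only in part.

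**Conclusion.** The point holds in limited form. On the natural reading, the T2 fruit-and-vegetable report in the intervention arm can be shaped by feedback given minutes earlier in the same session, while controls receive no personal feedback before T2. Physical activity is less directly exposed.

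The size is not known from the documents. The range of 0.1 to 0.2 SD is an assumption. If the whole shift were that large, it would equal 33% to 67% of the planned effect and would give a significant pooled T2 difference 37% to 90% of the time with no change in behaviour. This does not show that an observed effect would be an artefact.

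The conclusion rests on two readings: that T2 follows the Session 8 feedback, and that controls start at T2. On the second, Table 1 and Randomization (access after eight weeks) agree, but one sentence in Study design labels the controls' access T3. These passages must be reconciled. The change is worth making because it is nearly free and removes an avoidable difference between the arms.

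**What to change.** - State the order of screens in Session 8. Ask the T2 physical-activity and fruit-and-vegetable items once, at the start, before any feedback, norm comparison or figure, and generate the Session 8 feedback from those answers.
- Give controls the identical items in the same week, with the same neutral introduction.
- Word the conclusion as an effect on self-reported behaviour.
- State as a limitation that feedback in Sessions 1 to 7 may still influence reporting. Reordering removes only the same-session part.

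The cost is a small change of screen order and introductory text in the existing software, with no added measurement and one fewer recall question for the intervention arm. The downside is a possibly smaller apparent effect at T2.
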